#### Feasibility interviews

After the first follow-up assessment, 30 participants (10 from each arm) will be invited to participate in a semi-structured feedback interview. We considered the timing of this interview (whether to wait until after the final follow-up assessment) and ultimately decided that (at least for this feasibility study) we should keep interviews proximal to the main study procedures and intervention—particularly given the cognitive difficulties experienced by our participants and likelihood that later interviews would strain retrospective recall. Table 1 outlines the overall schedule of study assessments/procedures (including how the feedback interviews fit within this). We will use ‘maximum variation’ sampling to select a demographically and clinically diverse sample. We anticipate theoretical sufficiency with 30 participants but will extend recruitment if needed. We will use the Theoretical Framework of Acceptability to guide our interviews and analyses [71]. These interviews will allow SMART participants to feed-back on what they found helpful/unhelpful about intervention content and delivery, enabling us to further refine these. For those in control arms, interviews will explore their feelings about not receiving the intervention. All participants will be asked about the acceptability of research processes (including randomisation).

Participant feedback is often subject to the ‘halo effect’ produced by a perceived lack of independence of assessors. We will therefore train and supervise two patient-partners (PPs) to help us in this process, with support from the Research Fellow who is independent to intervention delivery. The process of involving PPs in conducting interviews engenders agency and capacity-building and enables PPs to bring their unique perspectives of being fellow patients, which may permit research-participants to be more open. We successfully used such PP engagement in the CRAMMS trial [16].

Up to 10 feedback interviews will be conducted by our PPs, who will be trained and supported to conduct them (by our PPI Lead), and the remainder will be conducted by the Research Fellow. PPs will have had DBS checks and will only conduct telephone/video-call interviews, following our Trust’s Volunteer Policy.

An interview schedule will be developed/piloted with the PPI group and PPs. Interviews will be audio-recorded with permission.

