### Participant timeline

Table 1 depicts the schedule of enrolment, interventions, and assessments for participants. Over the course of screening and baseline assessment procedures, consenting eligible patients will complete a cognitive assessment battery and questionnaires assessing the impact of living with MS, health-related quality of life, subjective cognitive difficulties, and service/resource use. After completing baseline assessments, participants will be randomly allocated to one of the three intervention arms (using block randomisation with varying block sizes to balance participant numbers across arms). Participants will complete follow-up assessments at 3 and 6 months post-randomisation; after the first follow-up assessment (>3 months post-randomisation) a sub-sample of participants will engage in feasibility-feedback interviews.

**Table 1 Tab1:** Schedule of enrolment, interventions, and assessments

Procedure/assessment	Screen 1	Screen 2	Baseline (0 months)	*Intervention period*	FU1 (3 months)	Interval b/w FUs	FU2 (6 months)
Enrolment:							
Initial eligibility screen	X						
Informed consent	X						
Demographic information	X						
Randomisation			X				
Interventions:							
SMART + TAU				X			
Active control training + TAU				X			
TAU				X			
Assessments:							
PDQ	X				X		X
Symbol Digit Modalities Test (SDMT)		X			X		X
RBANS			X		X		X
Generalized Anxiety Disorder Scale-7 (GAD-7)							
Patient Health Questionnaire-9 (PHQ-9)			X		X		X
Modified Fatigue Impact Scale–5-Item (MFIS-5)			X		X		X
Personal Questionnaire (PQ)			X		X		X
EQ-5D-5L			X		X		X
MS Impact Scale–29 (MSIS-8D; v.2)			X		X		X
ICECAP-A			X		X		X
Service- and resource-use questionnaire			X		X		X
Feedback interviews						X^a^	

*FU* follow-up, *Screen* screening appointment, *ICECAP-A* Investigating Choice Experiments Capability Measure for Adults, *TAU* treatment-as-usual

^a^With selected participants who will be consented prior to the interview

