### Randomisation and blinding

Participants will be individually randomised at baseline (after consent) in equal proportions to one of three groups (1:1:1 ratio) using block randomisation in permuted blocks of three and six.

Treatment allocation will be computer generated via the electronic trial database in Castor EDC (Castor Electronic Data Capture, available at: https://castoredc.com). Allocation sequence is concealed by Castor EDC until the randomisation of a participant. Castor EDC is used to assign participants to different groups.

Given the nature of the intervention, participants and the intervention-facilitating researchers will not be blinded. No unblinding procedures relating to potential adverse effects are therefore required. The assessments will be conducted by a Research Fellow who will be blind to treatment allocation. We will record any instances of unblinding to assess the feasibility of blinding outcome assessors to allocation.

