#### Follow-up measures

All participants will be assessed 3 and 6 months post-randomisation, using the same measures as at baseline. The assessing Research Fellow will be blind to allocation (any instances of unblinding will be recorded).

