### Data-Analysis

To specifically address the feasibility objectives of the proposed programme, our analysis will draw on multiple data sources—including qualitative data from post-trial feasibility interviews (see Table 1). Quantitative analyses (conducted using R and SPSS) will be primarily descriptive, focussing on key indicators of trial and cost-effectiveness analysis viability—including recruitment/attrition rates. Variability estimates will be computed for study outcomes and used to inform sample-size calculations for the definitive RCT (following DELTA [2] guidance [72]). To identify the signal of efficacy, we will estimate (group-level) effect sizes (with 95% CIs) and proportions achieving (individual-level) reliable and clinically significant changes. To handle incomplete outcome data when testing for the signal of efficacy (whether confidence intervals around effect sizes preclude clinically important differences) we will estimate effects using intent-to-treat linear mixed modelling—an available-case method that can accommodate missing datapoints. A Statistical Analysis Plan has been developed by the trial statistician, in consultation with the UoL Clinical Trials Unit, and will be applied with oversight from the TSC/DMEC. Qualitative data will be purposively analysed—applying Framework Analysis [73, 74] with support of Nvivo software—to understand participant study experiences and identify areas for development/revision towards a definitive trial. Framework Analysis is a structured analytical approach, enabling us to rapidly appraise data in relation to our a priori feasibility questions and deductive application of the Theoretical Framework of Acceptability [71].

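### As written, the Research Fellow who is to be blind at 6 months also interviews participants between the two follow-ups, so assessor blinding at the second follow-up is lost for those interviewed

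*Protocol article*

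**What the plan says.** **Who assesses.** Randomisation and blinding states: "The assessments will be conducted by a Research Fellow who will be blind to treatment allocation". It adds that instances of unblinding are recorded so that the feasibility of assessor blinding can be judged. Follow-up measures repeats the property: "The assessing Research Fellow will be blind to allocation (any instances of unblinding will be recorded". The same section gives the time points: "All participants will be assessed 3 and 6 months post-randomisation, using the same measures as at baseline".

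**Who interviews.** Feasibility interviews states: "After the first follow-up assessment, 30 participants (10 from each arm) will be invited to participate in a semi-structured feedback interview". On staffing it says "Up to 10 feedback interviews will be conducted by our PPs", "and the remainder will be conducted by the Research Fellow". The Research Fellow also supports the patient-partners, and is described there as independent of intervention delivery.

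**When.** Participant timeline states: "after the first follow-up assessment (>3 months post-randomisation) a sub-sample of participants will engage in feasibility-feedback interviews". Table 1 marks the interviews in the column for the interval between FU1 and FU2. Feasibility interviews reports that waiting until after the last follow-up was considered and not chosen, because later interviews would strain recall.

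**What is asked.** SMART participants comment on the content and delivery of the intervention. Participants in the control arms are asked how they felt about not receiving it.

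**A conflicting label.** Data-Analysis refers to "including qualitative data from post-trial feasibility interviews (see Table 1", and Table 2 also calls these interviews post-trial.

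**The concern.** An interviewer who asks these questions learns whether the participant had SMART. If the same person then tests that participant at 6 months, the blinding stated for FU2 does not exist for that participant. It is lost through a scheduled procedure, not by accident.

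Two outputs are at stake.

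- **SDMT and RBANS at FU2.** Both are performance tests that the article treats as focal outcomes, and the Fellow conducts the assessments. They feed the exploratory efficacy signal. Participants and facilitators are not blinded, so assessor blinding is the only blinding safeguard the article states.
- **The count of unblinding instances.** The trial collects it to learn whether assessors can be kept blind in a definitive trial. Unblinding caused by the interviews would be added to it and, unless separated, would make blinding look harder to maintain than it need be.

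**Working it through.** **Inputs**

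| Quantity | Value | Source |
|---|---|---|
| Arms | 3 | Trial design |
| Interviewees invited per arm | 10 | Feasibility interviews |
| Interviews by patient-partners | 0 to 10 | Feasibility interviews |
| Participants randomised | 60 | Sample size |
| Uptake of interview invitation | 100%, 80%, 60% | Assumption; not given |
| Retention at FU2 | 80% | Assumption; not given |

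**Step 1: the plan's own figure.** 3 × 10 = 30 invited, as stated.

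**Step 2: interviews left to the Fellow if all 30 take part.** Minimum 30 − 10 = 20; maximum 30 − 0 = 30.

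**Step 3: share of those randomised.** 20/60 = 33%; 30/60 = 50%.

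**Step 4: share of those assessed at FU2.** With 80% retention, 0.80 × 60 = 48. If every interviewee is retained, 20/48 = 42% and 30/48 = 63%.

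**Step 5: lower uptake.** The article gives 30 as the number invited, not the number interviewed.

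| Uptake | Interviews | Minimum by the Fellow | Share of 60 |
|---|---|---|---|
| 100% | 30 | 30 − 10 = 20 | 33% |
| 80% | 24 | 24 − 10 = 14 | 23% |
| 60% | 18 | 18 − 10 = 8 | 13% |

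The article also allows interview recruitment beyond 30, which would raise these counts. Exposure through the Fellow's support of the patient-partners could add to them and is not counted here.

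**Step 6: order of events.** FU1 (3 months), then interviews, then FU2 (6 months). FU1 precedes every interview and keeps its blinding. The retention criterion in Table 2 is tied to FU1 and is not touched.

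**Step 7: is it one person?** Randomisation and blinding speaks of a Research Fellow, Follow-up measures of the assessing Research Fellow, and Feasibility interviews of the Research Fellow. No second Fellow, separate FU2 assessor or separate interviewer is named. One person is the natural reading, but it is an inference from a shared job title.

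**The case against.** **Identity is inferred.** The word assessing in Follow-up measures could mark one Fellow off from another, and a condensed article may leave staffing to the full protocol. This stands as a limit on the point. It does not remove it: the article gives one role label to both tasks, and one sentence would settle the matter.

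**The trial is about feasibility.** Primary endpoints concern feasibility and the efficacy signal is exploratory. FU1, close to the end of the roughly 12-week intervention, is intact. The red criterion for efficacy uses the screening measures, which under the eligibility criteria are PDQ and SDMT. PDQ is self-reported by unblinded participants, so assessor blinding does little for it. All of this stands and lowers the severity.

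**The timing was reasoned.** The authors weighed later interviews and rejected them for recall, which matters in a cognitively impaired sample. That choice deserves respect, and the fix should not reverse it. The stated reasoning does not mention blinding, however.

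**The post-trial label.** A reader might take it to mean that the interviews follow FU2 and the conflict disappears. The text does not support that: Table 1 and the explicit rejection of waiting fix the timing before FU2. The label is loose wording.

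**Stronger readings.** A reader might infer that at least 20 participants are certain to be affected, that FU2 is unblinded for the whole sample, or that the blinding-feasibility result is lost. None of these follows. Twenty is a minimum only if all 30 invitees take part. Only participants the Fellow interviews are affected by the schedule itself. Interview-caused instances can be identified by participant and separated from the rest, and FU1 supplies an estimate free of interviews.

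**Conclusion.** The point holds in a limited form. The article states twice that the assessing Research Fellow is blind, and its interview plan does not deliver this at FU2 for participants the Fellow has interviewed. With full uptake that is 20 to 30 of 60 (33% to 50%). With 80% or 60% uptake, both assumed, the minimum is 14 or 8; extending interviews beyond 30 would push it up. The conclusion rests on there being one Research Fellow.

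The damage is confined mainly to SDMT and RBANS at FU2 and to an unseparated count of unblinding instances. FU1 and the retention criterion are unaffected. This should be fixed, but it does not undermine the primary feasibility aims.

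**What to change.** 1. Keep the interview timing. State that nobody who interviews a participant before FU2 assesses that participant at FU2. Use existing team members who are independent of intervention delivery, since the article wants that independence to limit halo effects. If two Research Fellows already share these tasks, say so.
2. If staffing does not allow this, state that only FU1 is fully assessor-blinded. Base the SDMT and RBANS efficacy signal on FU1 and label FU2 as partly unblinded.
3. In that case, also report unblinding caused by interviews separately from all other unblinding.
4. Reconcile the post-trial label in Table 2 and Data-Analysis with Table 1.

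The cost is a few sentences and some reallocation of roles or, under the fallback, a less favourable statement about blinding at FU2. It needs to be settled before the interviews begin, because unblinding cannot be undone.

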### Data management

All study staff and investigators will comply with the principles of the Data Protection Act (2018) in protecting the rights of study participants with regard to the collection, storage, processing, and disclosure of personal information and will uphold the Act’s/Regulations core principles. Each participant will be assigned a study identity number, for use on CRFs other trial documents and the electronic database. Personal data, research data and the linking code will be stored electronically in separate locations: this will include using encrypted digital files within password-protected folders and storage media. Personal information shall be stored separately to research data and will be kept secure and maintained. Personal data will be stored for 6 months following the end of the study, so that the Chief Investigator may provide participants with a summary of the research (should they wish to receive a copy). Data generated through this study will be available for inspection on request by the participating physicians, the University of Lincoln representatives, the REC, local R&D Departments and the regulatory authorities. Routine reviews of submitted data will be conducted to identify and follow up on missing data, inconsistent data, data outliers, and potential protocol deviations that may be indicative of systematic or significant errors in data collection and reporting at a site.

Questionnaire and eCRF data will be collected and stored using Castor EDC. Data gathered using the Castor EDC platform will only be accessible to the research team, with access rights managed by the database manager (ER). Participants will be given a unique study identifying code so that no identifiable information need to be entered.

### Data-Analysis

To specifically address the feasibility objectives of the proposed programme, our analysis will draw on multiple data sources—including qualitative data from post-trial feasibility interviews (see Table 1). Quantitative analyses (conducted using R and SPSS) will be primarily descriptive, focussing on key indicators of trial and cost-effectiveness analysis viability—including recruitment/attrition rates. Variability estimates will be computed for study outcomes and used to inform sample-size calculations for the definitive RCT (following DELTA [2] guidance [72]). To identify the signal of efficacy, we will estimate (group-level) effect sizes (with 95% CIs) and proportions achieving (individual-level) reliable and clinically significant changes. To handle incomplete outcome data when testing for the signal of efficacy (whether confidence intervals around effect sizes preclude clinically important differences) we will estimate effects using intent-to-treat linear mixed modelling—an available-case method that can accommodate missing datapoints. A Statistical Analysis Plan has been developed by the trial statistician, in consultation with the UoL Clinical Trials Unit, and will be applied with oversight from the TSC/DMEC. Qualitative data will be purposively analysed—applying Framework Analysis [73, 74] with support of Nvivo software—to understand participant study experiences and identify areas for development/revision towards a definitive trial. Framework Analysis is a structured analytical approach, enabling us to rapidly appraise data in relation to our a priori feasibility questions and deductive application of the Theoretical Framework of Acceptability [71].

### Monitoring

Study conduct will be governed by a Joint Trial Steering Committee and Data Monitoring (and Ethics) Committee (TSC/DMEC)

#### Joint TSC/DMEC

The TSC/DMEC will have an independent chair, two clinical/academic members, two Patient and Public Involvement (PPI) members, and an independent statistician. The TSC/DMEC will provide independent oversight of the study and will meet (in person or by teleconference) at least every 6 months with more frequent meetings as necessary. This joint committee will safeguard the interests of trial participants—with particular reference to safety and the efficacy of the intervention—monitor the overall progress and conduct of the trial, monitor the outcome data regularly during data collection, and assist and advise the investigators so as to protect the validity and credibility of the trial.

#### Harms

Adverse events of participation in this study may be (1) exacerbation of MS-related fatigue through engagement with the intervention and study procedures and (2) elevated distress if participants find that they are not performing as well as they think they should during cognitive assessments. There are no serious adverse events anticipated with participating in this study. In practice, with respect to (1), participants will be able to withdraw at any point—one purpose of this (feasibility) study is to understand whether the intervention and study procedures are acceptable, and withdrawal due to perceived burdensomeness/exacerbation of fatigue will be informative for addressing our feasibility aims and informing future intervention and trial design. With respect to (2), this is considered to be a low-probability risk, causing minimal distress (based on our experiences of running similar trials (e.g. CRAMMS [10.1186/ISRCTN09697576]) but any such distress will be managed by the assessing psychologists who are qualified to deal with distress in an appropriately compassionate manner—and will make necessary referrals (to the participant’s GP) as needed.

All adverse events will be recorded and closely monitored until resolution, stabilisation, or until it has been shown that the study treatment/intervention is not the cause.

Participant removal from the study due to adverse events. Any participant who experiences an adverse event may be withdrawn from the study at the discretion of the Investigator.

### Auditing

Compliance with the protocol will be assessed throughout using central monitoring techniques. This will be achieved through routine reviews of submitted data to identify and follow-up on missing data, inconsistent data, data outliers, and potential protocol deviations that may be indicative of systematic or significant errors in data collection and reporting at a site. An interim analysis will be conducted by the TSC/DMEC to check that the project is operating appropriately—examining consent, retention, and completeness of data. The TSC/DMEC can make a recommendation for continuation/stopping or highlight any concerns or areas that may need attention (e.g. changes in recruitment practices, strategies to improve retention, or similar).

Accidental protocol deviations may occur at any time. Accidental protocol deviations will be adequately documented on the relevant forms and reported to the Chief Investigator and Sponsor immediately. Deviations from the protocol which are found to frequently recur are not acceptable, these will require immediate action and could potentially be classified as a serious breach.

### Dissemination policy

Dissemination will be multipronged to inform a wide audience of patients, carers, and clinicians.Trial participants will be offered a lay summary of findings.The wider public will be informed through Trust- and study-specific websites, and via press offices for the collaborating institutions—care will be taken to reflect the early staging of the research, focus on feasibility, and conditionality of potential implications.We will submit findings for presentations at relevant meetings: informing the academic community and fostering interest from potential collaborators for the definitive RCT (extending the network of research sites).We will publish feasibility results in (open access) peer-reviewed national and international journals and professional newsletters.Along with our PPI Advisory Panel, we will co-write for newsletters/webpages of relevant charities that reach patients and carers directly.

Regarding outcomes, study results will directly inform protocol development for a fully powered, definitive RCT. Should this RCT demonstrate that SMART is clinically effective, there is a clear trajectory to benefit for patients, carers, and the NHS: increasing the availability and accessibility of treatment/self-management options for cognitive rehabilitation in MS—and thereby enabling improved service provision and reducing demands on services to manage sequelae of untreated cognitive deficits. If clinically effective, the low-resource nature of the intervention makes SMART more likely to be implemented—and a full cost-effectiveness analysis in the future RCT will indicate the relative value for money to the NHS/Personal Social Services of SMART. The remote accessibility of SMART (as an online intervention) is particularly beneficial in the context of COVID-19 and would enable swift and scalable implementation—consistent with the NHS digital healthcare agenda.

